### Statistical considerations

#### Primary analysis

To determine whether the cancer detection rate is higher in the intervention group than in the control group, a two-tailed analysis will be conducted using a multilevel logistic regression model. Levels in the model will be case, batch and centre. To prevent overfitting, each level will be included in the final model only if it explains a sufficient portion of the variability and improves model fit. The intervention may be more effective in certain subgroups, particularly younger women, women whose cases are read at the very beginning or end of the batch and the first batches to be examined in a workday. These subgroups will be analysed separately as specified in the statistical analysis plan and agreed by the Trial Steering Committee.

Analysis will be conducted as intention to treat, with all cases randomised included in the analysis. Missing data through loss to follow-up will occur in both groups for women who are recalled from screening but either did not attend the follow-up appointment or for whom no records exist in the database concerning the results of that appointment. Multiple imputation and sensitivity analyses to examine the effects of any missing data on the model will be considered if appropriate.

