**Methods/Design:**

The CO-OPS study is a pragmatic, multi-centre, two-arm, double blind cluster randomised controlled trial of a computer software intervention designed to reduce the effects of a vigilance decrement in breast cancer screening. The unit of randomisation is the batch. Intervention batches will be examined in the opposite order by the two readers (one forwards, one backwards). Control batches will be read in the same order as one another, as is current standard practice. The hypothesis is that cancer detection rates will be higher in the intervention group because each readers’ peak performance will occur when examining different women’s mammograms. The trial will take place in 44 English breast screening centres for 1 year and 4 months. The primary outcome is cancer detection rate, which will be extracted from computer records after 1 year of the trial. The secondary outcomes include rate of disagreement between readers (a more statistically powerful surrogate for cancer detection rate), recall rate, positive predictive value, and interval cancer rate (cancers found between screening rounds which will be measured three years after the end of the trial).

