### Trial summary

The trial is a pragmatic, multicentre, two-arm, double-blind, cluster randomised controlled trial of a computer software intervention designed to reduce the effects of a vigilance decrement in breast cancer screening. The intervention changes the order in which the readers examine the batches of mammograms. The centres will be NHSBSP centres with digital mammography equipment. A cluster for randomisation comprises a batch of mammograms (approximately 30 to 50 women’s mammograms). Intervention batches will be examined in the opposite order by the two readers (one in appointment order and one in reverse appointment order). Control batches will be read in the same order as one another as is current standard practice. The unit for analysis is the individual woman’s outcome.

Standard practice is for both readers to read the batch of mammograms in the order in which the women were booked in for their appointments. In the control group, both readers will read each batch in the same order as one another, but this may be in appointment order or in reverse appointment order (↓↓ or ↑↑). In the intervention group, both readers will read the mammograms in the order opposite one another (↓↑ or ↑↓). This design blinds the readers because if they read in the reverse order, they will not know if they are reading the intervention or control group. The study software which will be used to run the trial will be embedded in the National Breast Screening Service (NBSS) software system in every English breast screening centre as part of routine updating of the NBSS system.

The pilot study will be conducted in three screening centres for 2 weeks to ascertain practical issues with implementation and to test the data collection tool, which will extract the results from the screening centres’ electronic database (NBSS). Concurrently, a survey of all English breast screening centres will be conducted to ascertain key characteristics relevant to the trial which may differ between centres, such as the method of arbitration used. These details will be described in the report and considered in the statistical analysis of the trial to ascertain whether the effectiveness of the intervention is affected by these characteristics.

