#### Secondary analyses

To determine whether the disagreement rate between readers, interval cancer rate and recall rate are different between the intervention and control groups (secondary aims 1, 2 and 3), the same methods as described for the primary analysis above will be used. The PPV of cancer detection in each study arm will be calculated as the proportion of women recalled who are found to have cancer (secondary aim 3).

The effects of the trial introducing the reverse reading order (secondary aim 5) will also be analysed. The recall and cancer detection rates for the two reading groups which make up the control arm will be compared (↓↓ compared to ↑↑). Models will be constructed in the same way as the primary analysis, but using reading order, not trial group membership, as the predictor of cancer detection rate and recall rate.

To generate secondary outcome 4 (estimates of cost-effectiveness), the primary outcome from the trial will be used as an input into a health economic model of breast cancer screening. This model will be developed by expanding an earlier breast cancer model described by Campbell *et al*. [12] and will predict lifetime costs and effects for both the intervention and control arms. The model simulates the underlying breast cancer disease process according to prognosis upon presentation and includes adjuvant therapies, the long-term risk of recurrence (both local and metastatic) and treatment and long-term survival following recurrence. It will be used to model the changes in costs, life-years and quality-adjusted life years brought about by a potential change in the cancer detection rate.

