### Power and sample size

Currently, 14,700 cancers are detected by screening each year, and the cancer detection rate is 7.8 per 1,000 women screened [3]. Detection of one extra cancer case per 2,000 women screened would increase the cancer detection rate to around 8.3 cancers per 1,000 women screened. To detect this change of 0.5 cancers per 1,000 women using a two-tailed test at 80% power and 5% significance, 501,361 women are required in each arm.

As randomisation occurs at the batch level, however, collected data are clustered and this must also be taken into consideration. The sample size of a clustered study must be increased by the design effect (DE), which is calculated as *DE* = 1 + (*m* - 1)*ρ* for a given intraclass correlation coefficient (ICC; *ρ*) and cluster size (*m*). The ICC was calculated using previous data in a logistic binomial Gaussian model (method B) with 1,000 Monte Carlo simulations [13]. Hence, using the ICC of 0.002 and a cluster (batch) size of 40 women produces a DE of 1.09, increasing the sample size required to 546,890 in each arm.

There is no adjustment for crossover, because once the intervention is applied to a screening centre, each batch will automatically be randomly assigned to the intervention or control group by the NBSS computer system and the intervention will be applied automatically by the same system. A woman could be lost to follow-up if her NBSS records have not been updated or if she is recalled from screening for further tests and does not attend her follow-up appointment. This is uncommon, however, so we have assumed low dropout rates of 3,500 women in each arm, inflating the sample required to 550,390 in each arm. Therefore, as detailed in Figure 1, the overall sample size required is for 1,100,780 women, or 44 breast screening centres for 1 year (On the basis that in England there are 82 centres each screening around 25,000 women per year).

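### The rule for keeping levels in the multilevel model also covers batch, the unit of randomisation, so the text permits between-arm tests that ignore the clustering

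*Protocol article*

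**What the plan says.** The abstract of the protocol article states the design: "The unit of randomisation is the batch". The Trial summary adds that "The unit for analysis is the individual woman’s outcome", so randomisation and analysis are at different levels and the analysis has to bridge them.

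Under Primary analysis, "a two-tailed analysis will be conducted using a multilevel logistic regression model", and "Levels in the model will be case, batch and centre". The next sentence, which gives prevention of overfitting as its reason, qualifies this: "each level will be included in the final model only if it explains a sufficient portion of the variability and improves model fit". The rule applies to each level, names no exception for batch, and joins its two conditions with an 'and'.

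Under Secondary analyses, for disagreement, interval cancer and recall, "the same methods as described for the primary analysis above will be used". The comparison of the two control reading orders is to be modelled in the same way.

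Under Power and sample size the protocol takes the opposite position on clustering: "As randomisation occurs at the batch level, however, collected data are clustered and this must also be taken into consideration". It then raises the requirement from 501,361 to 546,890 women per arm.

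**The concern.** When batches are randomised, variation between batches is part of the error of the treatment contrast. That follows from the design and does not depend on how large the estimated batch variance turns out to be. A rule that can remove batch after the data are seen makes this part of the error optional. If batch is removed and nothing else accounts for it, standard errors are too small and the test rejects too often.

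The stated reason is weak for this level. A batch random intercept adds one variance parameter, and 1,100,780 women in batches of 40 give about 27,500 batches from which to estimate it.

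The rule also reaches beyond the primary outcome. The Discussion says that disagreement may have to become the primary outcome if recruitment falls short, and the same methods apply there. The whole batch shares its two readers, so correlation of recall decisions within a batch is plausible.

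**Working it through.** **Inputs (Power and sample size; Trial summary).** Detection rates 7.8 and 8.3 per 1,000; two-sided 5%; 80% power; 501,361 per arm before clustering; intraclass correlation (ICC) 0.002; batch size m = 40, with batches of about 30 to 50; stated design effect (DE) 1.09; 546,890 per arm after clustering; 1,100,780 women in total.

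**Step 1: reproduce the plan's figures.**
- The two-proportion formula (pooled, no continuity correction) gives 501,398 per arm, against 501,361 stated. This agrees.
- DE = 1 + (m − 1) × ICC = 1 + 39 × 0.002 = 1.078, which gives 501,361 × 1.078 = 540,467 per arm. This is 1.2% below the stated 546,890.
- The stated figures imply DE = 546,890 / 501,361 = 1.0908, so an unrounded ICC of 0.0908 / 39 = 0.00233. Rounding of the ICC would explain the gap. Both values are carried forward.

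**Step 2: type I error if batch is ignored.** The naive standard error is too small by a factor √DE, so the actual two-sided error is 2 × [1 − Φ(1.96 / √DE)].

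| DE | 1.96 / √DE | Type I error |
|---|---|---|
| 1.078 | 1.888 | 5.9% |
| 1.09 | 1.877 | 6.0% |
| 1.0908 | 1.877 | 6.1% |

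Over batch sizes 30 to 50 and ICC 0.002 to 0.00233, the range is 5.7% (DE 1.058) to 6.3% (DE 1.114).

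A beta-binomial simulation under the null (27,519 batches of 40, 5,000 replicates per ICC) gave 6.3% and 6.0% with batch ignored, at ICC 0.002 and 0.00233. With a cluster-adjusted variance it gave 5.1% and 4.9%.

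**Step 3: how likely is batch to be dropped?** In the same simulation, a one-sided 5% test for batch variance stood in for the fit criterion.

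| ICC | Batch kept | Type I error if batch ignored (formula, m = 40) |
|---|---|---|
| 0.0002 | 25% | 5.1% |
| 0.0004 | 58% | 5.2% |
| 0.001 | 99.7% | 5.5% |
| 0.002 | 100% | 5.9% |

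On fit alone, batch is often dropped only where dropping it costs about 0.2 percentage points or less. To reach about 6%, batch would have to improve fit and still be removed because the portion of variability it explains was judged too small.

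**Step 4: how small would that portion look?** It depends on the scale. On the proportion scale an ICC of 0.002 is 0.2% of variance. The planned model is logistic. Solving for the normal random intercept that gives a proportion-scale ICC of 0.002 at 7.8 per 1,000 yields a batch variance of about 0.23. Against the usual logistic residual of π²/3 = 3.29, the share is 0.23 / (0.23 + 3.29), about 6.6%. The article does not say which scale is meant.

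**Step 5: secondary outcomes.** No ICC is given for disagreement or recall. As an illustration only, assumed ICCs of 0.005, 0.01 and 0.02 at m = 40 (DE 1.195, 1.39 and 1.78) would give 7.3%, 9.6% and 14.2% if batch were ignored.

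**The case against.** The strongest reply is that modelling batch is the default. The model lists batch as a level, the sample size pays for it, and the Methods commit to reporting by the guidance for cluster randomised trials. Dropping batch is a permitted exception, and Step 3 shows that a fit test would not produce it at the planned ICC. This stands, and it limits the point to what the text allows. A reader might infer that the trial will be analysed as if women had been individually randomised; the documents do not support that.

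A second reply is that the meaning of a sufficient portion, and any fallback to robust standard errors, may be set in the statistical analysis plan, which is not shown. That also stands, so the absence of a threshold is not counted here as a fault. What remains is that the protocol states a rule and the rule covers the unit of randomisation. A threshold in the analysis plan would define that rule without exempting batch from it.

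Third, about 6% is an upper figure for the planned ICC at batch size 40. Batches are randomised within centres, so if centre is kept in the model, any part of the 0.002 that lies between centres does not inflate the error.

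A reader might also take 0.2% of variance as a value bound to be judged negligible, or take the 7% to 14% figures as the likely error for recall and disagreement. Neither follows. On the log-odds scale the share is about 6.6%. The secondary figures rest on assumed ICCs, and at those ICCs batch would be the least likely to be dropped.

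**Conclusion.** The point holds as an inconsistency in the stated rule. The Primary analysis section makes it optional to model the unit of randomisation, while the sample size section treats the clustering as something that must be taken into account.

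If batch were dropped from the primary test, the two-sided type I error would be at most about 6% instead of 5%. This assumes batches of 40, a within-centre ICC of 0.002 to 0.00233, and no other correction for clustering. The probability of that outcome cannot be derived from the documents. It is negligible on fit alone and otherwise depends on how the variability condition is applied. For disagreement and recall the size is unknown.

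This should be fixed, because a confirmatory test should not depend on a data-driven choice about whether to respect the randomisation. With about one percentage point at stake, it does not threaten the trial's validity.

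**What to change.** Exempt batch from the retention rule. Suggested wording for the protocol and the analysis plan: 'A batch-level random intercept (or batch-clustered robust standard errors if the model does not converge) is kept in every between-arm and reading-order comparison, primary and secondary, whatever its estimated variance or its effect on model fit. Simplification on grounds of fit is limited to levels other than the unit of randomisation.'

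The cost is one or two sentences. The sample size already carries the design effect and need not change. Where batch would otherwise have been dropped, standard errors widen by about 4% (√1.078 = 1.038; √1.0908 = 1.044). Elsewhere nothing changes.

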#### Secondary analyses

To determine whether the disagreement rate between readers, interval cancer rate and recall rate are different between the intervention and control groups (secondary aims 1, 2 and 3), the same methods as described for the primary analysis above will be used. The PPV of cancer detection in each study arm will be calculated as the proportion of women recalled who are found to have cancer (secondary aim 3).

The effects of the trial introducing the reverse reading order (secondary aim 5) will also be analysed. The recall and cancer detection rates for the two reading groups which make up the control arm will be compared (↓↓ compared to ↑↑). Models will be constructed in the same way as the primary analysis, but using reading order, not trial group membership, as the predictor of cancer detection rate and recall rate.

To generate secondary outcome 4 (estimates of cost-effectiveness), the primary outcome from the trial will be used as an input into a health economic model of breast cancer screening. This model will be developed by expanding an earlier breast cancer model described by Campbell *et al*. [12] and will predict lifetime costs and effects for both the intervention and control arms. The model simulates the underlying breast cancer disease process according to prognosis upon presentation and includes adjuvant therapies, the long-term risk of recurrence (both local and metastatic) and treatment and long-term survival following recurrence. It will be used to model the changes in costs, life-years and quality-adjusted life years brought about by a potential change in the cancer detection rate.

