The trial will last 16 months in 44 centres and will include all women attending routine digital mammography screening during the study period. The data gathered during the first 12 months (1.1 million women) will be derived from the NBSS database to determine whether the intervention has increased the cancer detection rate. These data will include all items for the primary and secondary analyses, with the exception of interval cancer rate. The interval cancer data will be collected 3 years after the end of the study period to ascertain whether there has a been a decrease in the rate of interval cancers and therefore whether the intervention reduced the number of cancers missed at screening.

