### Trial aims and outcomes

The primary aim of the trial is to determine whether presenting the cases to the first and second readers in the order opposite one another increases the cancer detection rate (true-positive rate). The secondary aims and outcome measures of the trial are as follows:

1. Is there a difference in the number of disagreements between readers in each study arm? This is the proposed mechanism by which an increase in cancer detection rate occurs and therefore acts as a surrogate outcome, particularly if the effect size is smaller than anticipated or recruitment targets are not met. The rate of disagreement refers to the proportion of cases for which one reader thought the case should be recalled and the other reader thought the case should not be recalled.

2. Is there a difference in 3-year interval cancer rate in each study arm? Furthermore, as the interval cancer rate can be considered an approximation of the false-negative rate, is this change (if any) concurrent with changes in the cancer detection rate between study arms (primary outcome)? The interval cancer rate is measured as the rate of cancers detected symptomatically in the 3 years subsequent to screening and therefore will be collected 3 years after the trial implementation is complete.

3. Do the recall rate and positive predictive value (PPV) differ between the study arms?

4. With regard to NHS considerations, is the intervention cost-effective when compared with the control arm? The lifetime cost-effectiveness of the intervention will be modelled using the primary outcome from the trial. Are there any effects introduced by the trial methodology? Specifically, are the cancer detection and recall rates affected by introducing reverse reading order? The cancer detection rate and the recall rate for both versions of the control arm (↓↓ and ↑↑) will be compared to measure any adverse effects of reading in reverse order.

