## Discussion

The experimental design is between subjects, so readers will not be burdened with reading cases twice (once in each experimental condition). This design has lower statistical power than a within-participant approach, however, so recruitment targets are high to achieve 80% power. Sensitivity analysis for the estimate of effect size indicates that it is very sensitive to small changes in effect size. If the effect size is as low as 200 extra cancers detected per year in England, it may still be considered clinically significant, but overall sample size would need to be 14 million women to detect such an effect. Achieving a sample of this size would be unrealistic; therefore, there is a risk of the trial being underpowered. However, an effect size of 200 extra cancers detected in England each year would be detectable in the form of a surrogate for cancer detection rate, which is the rate of disagreements between readers. This parameter is included as a secondary outcome. If recruitment targets are not met, then the rate of disagreements, as a surrogate for cancer detection rate, may have to be used as the primary outcome.

One possible mechanism for harm from the intervention is associated with reading the cases in reverse appointment order, which is not currently standard practice. To blind the readers to group allocation, however, reading in reverse appointment order is present equally in the intervention and control groups, so a two-tailed test would not detect this harm. Therefore, a secondary analysis of recall rate and cancer detection rate of cases read in appointment order and reverse appointment order will be carried out to determine whether reading a batch in reverse appointment order affects performance.

This study is a pragmatic multicentre, two-arm, double-blind, cluster randomised controlled trial of a computer software intervention designed to reduce the effects of a vigilance decrement in breast cancer screening. The intervention and randomisation are applied automatically using computer software, thus reducing the cost of running the trial and limiting the possibility of allocation and treatment bias. This study design also reduces the administrative burden on participating centres, thus removing one of the barriers to participation. The trial is double-blinded because neither the women screened nor the readers will be aware of whether each batch is in the intervention or control group.

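### The check for harm from reverse-order reading compares the two control subgroups on recall and cancer detection only; the planned 3-year interval cancers should be added alongside them

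*Protocol article*

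**What the plan says.** The Discussion names the risk: "One possible mechanism for harm from the intervention is associated with reading the cases in reverse appointment order, which is not currently standard practice". It adds that reverse reading is equally common in both arms, so the comparison of arms would not reveal such harm.

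The check is described in three places of the protocol article:

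- Trial aims and outcomes, within item 4, asks: "Specifically, are the cancer detection and recall rates affected by introducing reverse reading order". The two rates in the forward-forward and reverse-reverse control groups "will be compared to measure any adverse effects of reading in reverse order".
- Secondary analyses, where it is called secondary aim 5: "The recall and cancer detection rates for the two reading groups which make up the control arm will be compared". The models follow the primary analysis, "using reading order, not trial group membership, as the predictor of cancer detection rate and recall rate".
- Discussion: "a secondary analysis of recall rate and cancer detection rate of cases read in appointment order and reverse appointment order will be carried out". This sentence names the same two outcomes but does not mention the control subgroups.

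On interval cancers, Trial aims and outcomes says that "the interval cancer rate can be considered an approximation of the false-negative rate". Trial summary plans their collection 3 years after the study period, to show whether their rate has fallen and "therefore whether the intervention reduced the number of cancers missed at screening". Under Secondary analyses they are compared between intervention and control only.

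**The concern.** If reading in reverse makes readers less accurate, the consequence for women is missed cancers. The protocol has an outcome that it uses for missed cancers, but it assigns that outcome only to the comparison of arms, which it says is blind to this harm. The one comparison that can show the harm is left with recall and detection. The two outcomes are named in the text, so this is a choice that the protocol has fixed and not a detail left open for the analysis plan.

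Each control subgroup is half of one arm, so the detection comparison is much less powerful than the primary analysis. A null first-year result could be reported as showing no effect of reading order, while planned data bearing on the same question go unused. An interval cancer comparison by reading order added after the results are known could also be dismissed as post hoc.

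**Working it through.** **Inputs from the protocol.** Power and sample size: detection rate 7.8 per 1,000, target difference 0.5 per 1,000, two-sided 5%, 80% power, 501,361 women per arm before clustering, stated design effect (DE) 1.09, 550,390 per arm in total. Recruitment and randomisation: equal allocation to four groups. Background: interval cancer rate achieved, about 3 per 1,000.

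**Assumption.** The share *f* of missed cancers that surface as interval cancers within 3 years is not in the protocol, so a range is shown.

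**Step 1, the plan's own figure.** Two proportions, 0.0078 and 0.0083, pooled variance under the null: n = 501,398 per arm, against the stated 501,361. The figure reproduces. The stated ICC and batch size give DE = 1 + 39 × 0.002 = 1.078, not 1.09. The stated 1.09 is used below, and the choice moves the detection power only between 53% and 54%.

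**Step 2, size of each control subgroup.** 550,390 / 2 = 275,195 women. Effective number: 275,195 / 1.09 = 252,472.

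**Step 3, detection, as planned.** Take the trial's own effect size in the harmful direction, 7.8 against 7.3 per 1,000.

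- SE = √[(0.0078 × 0.9922 + 0.0073 × 0.9927) / 252,472] = 0.244 per 1,000
- z = 0.5 / 0.244 = 2.05
- Power = Φ(2.05 − 1.96) = about 54%

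**Step 4, interval cancers for the same loss.** The comparison is 3.0 against 3.0 + 0.5*f* per 1,000, with the same formula. At *f* = 100%, SE = 0.160 per 1,000, z = 0.5 / 0.160 = 3.12 and power is about 88%.

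**Step 5, programme sensitivity, screen-detected / (screen-detected + interval).** Forward-forward: 7.8 / 10.8 = 72.2%, among 275,195 × 0.0108 = 2,972 cancers. Reverse-reverse: 7.3 / (7.3 + 3.0 + 0.5*f*). At *f* = 100% this is 7.3 / 10.8 = 67.6%. With the number of cancers divided by 1.09, z = 3.73 and power is about 96%.

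| Assumed share surfacing | Interval rate, per 1,000 | Power, interval rate | Sensitivity | Power, sensitivity | Power, detection |
|---|---|---|---|---|---|
| 100% | 3.0 v 3.5 | 88% | 72.2% v 67.6% | 96% | 54% |
| 75% | 3.0 v 3.375 | 66% | 72.2% v 68.4% | 87% | 54% |
| 50% | 3.0 v 3.25 | 36% | 72.2% v 69.2% | 69% | 54% |
| 25% | 3.0 v 3.125 | 12% | 72.2% v 70.0% | 43% | 54% |

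The interval rate overtakes detection when roughly two thirds of missed cancers surface, and sensitivity does so at somewhat over one third.

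**Step 6, smallest difference detectable with 80% power.** (1.96 + 0.84) × √[2p(1 − p) / 252,472] gives about 0.69 per 1,000 for detection (p = 0.0078) and about 0.43 per 1,000 for interval cancers (p = 0.003).

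**The case against.** The strongest reply is that the planned check is already sound. Batches are randomised to the four groups, so the number of cancers present is balanced in expectation. Lower detection in the reverse-reverse group would be direct randomised evidence of missed cancers. Chance variation in how many cancers are present is already in the standard error, so it costs precision and does not bias the comparison. This stands. A reader might infer that the harm is never assessed on an outcome that reflects missed cancers, but the design does not support that.

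Second, interval cancers are not uniformly the better test. At low surfacing shares detection has more power than either alternative. Programme sensitivity is not an outcome of this protocol, and its denominator depends on what is found, so with incomplete surfacing it understates the loss. This also stands. It rules out resting the conclusion on the 3-year result alone or treating first-year detection as merely provisional.

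Third, a reader might infer that this comparison decides whether the intervention is safe to adopt. It does not. Under the intervention one reader is reversed; reverse-reverse is a control allocation that serves blinding. Trial aims and outcomes presents the check as one on effects of the trial methodology.

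Last, an analysis plan that is not shown might contain this comparison. That is possible, but the protocol names the outcomes of this check explicitly and assigns interval cancers to the arm comparison.

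**Conclusion.** The point holds as a gap in completeness and power, not as an error of validity. For a loss as large as the gain the trial is designed to find, the detection comparison by reading order would give a non-significant result nearly half the time (about 54% power). The protocol plans to collect a complementary outcome but does not use it in the only comparison where this harm could appear.

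How much interval cancers would add rests on the assumed surfacing share, and on about 3 interval cancers per 1,000, the stated design effect and full recruitment. Across shares from 100% down to 25%, power runs from about 88% to 12% for the interval rate and from about 96% to 43% for sensitivity. The primary result is unaffected. Severity is minor to moderate.

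**What to change.** Keep the first-year comparison of recall and detection as planned. In Trial aims and outcomes and in Secondary analyses, add for the planned 3-year analysis:

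- the forward-forward versus reverse-reverse comparison of interval cancer rate, with the same model and a 95% confidence interval;
- screen-detected / (screen-detected + interval) by the same two groups, as a supporting measure.

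State that the detection and interval results will be interpreted together, and that a null first-year result alone will not be read as absence of harm from reverse reading.

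The cost is two more model fits on data already planned for collection and one additional secondary comparison to interpret. The full statement on reading order would be completed at 3 years, with the first-year results still reported on time.
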